## Methods

### Study Design

An interrupted time series design with a convergent qualitative component is proposed to test the effectiveness of the intervention. The intervention consists of observing the same dependent variable over time, with a break in the series of observations corresponding to the introduction of an intervention. If the intervention is effective, a change in the series’ pre- and postintervention averages can be observed [45]. Moreover, such design will accommodate pre-existing trends and control for possible variations within and among sites (eg, rehabilitation treatment efficacy, low adherence to treatment plan, and team composition). This study was registered at ClinicalTrials.gov (NCT04440215).

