### Sample Size Estimates

We calculated the sample size for a univariate comparison of the primary outcome between the two study groups at 12 weeks. The required sample size was calculated using G*Power (version 3.1.9.4; Heinrich-Heine-Universität Düsseldorf) based on a conservative estimated effect size of the intervention (Cohen *d*) of 0.4. This sample size was calculated assuming the following: (1) a two-sided type I error probability of 5% and a power of 80%, (2) a duration of 12 weeks, (3) a 2:1 ratio of intervention to control group participants, (4) two study groups, (5) a <5% loss to follow-up, and (6) intracluster correlations of 0.10. Therefore, 330 participants will be recruited: 110 and 220 participants in the control and intervention groups, respectively.

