### Analyses

Baseline site and participant characteristics will be summarized descriptively. Patient outcomes will be summarized by group and site. Statistical analysis of the data will follow intention-to-treat principles. A linear mixed model will be used, with individuals’ data nested into a study site, to isolate the effect of the intervention on both clinical and process outcomes from other changes that may take place during the trial. Key contextual factors, such as patient’s sex and age, state of employment prior to stroke, stroke severity, concomitant rehabilitation treatments received outside the rehabilitation center, and time since stroke event (in days), will be considered in regression models as potential confounders. Interaction terms will be included in the model for any statistically significant contextual factors. Presence of dichotomous stroke outcomes (eg, dizziness) will be compared between study groups using a chi-square test. Multiple imputation will be considered if missing data represent more than 10% of a given variable. Sensitivity analysis will be conducted to assess the impact of missing data on estimates of intervention effects with a multiple imputation statistical technique and without imputation (ie, available case analyses), as well as for outlying observations.

Interviews and treatment plan meetings will be fully transcribed. A descriptive analytical approach will be used to develop a framework of organizational factors leading to a successful telerehabilitation intervention, both at the patient and professional levels. Audio recordings and transcripts will be reviewed simultaneously to assess validity of the transcription process and will be analyzed using an iterative approach [64]. Data saturation will be determined as defined by Constantinou et al [65]. This will be followed by an intersite analysis to identify what is common between the sites examined and what is specific to certain sites, and to compare the different configurations between sites. Finally, matrices with contextual factors will be generated to identify particular patterns [66].

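### Adding interactions for any significant contextual factor lets the data choose the primary model and, unless factors are centred or an averaged effect is reported, moves the intervention coefficient away from the average effect

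*Protocol article*

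**What the plan says.** The Analyses section describes one linear mixed model, with patients nested in site, whose purpose is "to isolate the effect of the intervention on both clinical and process outcomes from other changes that may take place during the trial". It names six contextual factors (sex, age, employment before the stroke, stroke severity, rehabilitation received elsewhere, time since stroke) as examples, so the list is open. These "will be considered in regression models as potential confounders". The next sentence is the rule at issue: "Interaction terms will be included in the model for any statistically significant contextual factors".

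Two other sections show which effect is wanted. Study Design says that, if the intervention works, a change in the series' "pre- and postintervention averages can be observed". Sample Size Estimates says: "We calculated the sample size for a univariate comparison of the primary outcome between the two study groups at 12 weeks". Both describe one average difference between phases.

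The article does not call the interactions secondary or exploratory. It names no interaction-free primary model and no averaged contrast.

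**The concern.** The rule is worded as a commitment and applies to the model that is meant to deliver the intervention effect. Two things follow if the interactions are intervention-by-factor terms triggered by the factor's own p-value.

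- **The trigger does not match the term.** A significant factor is prognostic. That says nothing about whether the intervention works differently across its levels. Age or stroke severity could well predict rehabilitation minutes, and would then bring in interactions with no sign of effect modification.
- **The meaning of the coefficient can depend on the data.** With an intervention-by-factor term in the model, the intervention coefficient is the effect where that factor equals zero or its reference level. Which factors this applies to depends on which p-values were small.

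At stake is whether the reported primary estimate is the average effect that the trial was designed and sized to estimate, and how precisely it is estimated. The phases are sequential and not randomised, so the result leans on this model more than a randomised comparison would.

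**Working it through.** **Inputs from the article.** Cohen d 0.4, two-sided 5%, 80% power, 2:1 ratio, loss under 5%, intracluster correlation 0.10, five sites, 110 control and 220 intervention patients, six named factors. **Assumed, because the article gives none:** a 5% selection level, and all factor distributions and effects.

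**1. The plan's own figure.** Control n = (1 + 1/2)(1.96 + 0.8416)²/0.4² = 73.6, so 74. Loss: 74/0.95 = 77.9, so 78. With a design effect of 1 + (5 − 1) × 0.10 = 1.4, 78 × 1.4 = 109.2, so 110 control, 220 intervention and 330 in total. The match needs a cluster size of 5, which the article does not state. What matters here is that the calculation is for a two-group difference with no interactions.

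**2. Reference precision.** On the SD = 1 scale, ignoring site and covariates, SE = √(1/110 + 1/220) = 0.117. Power for d = 0.4 is 0.93.

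**3. One interaction added, no true effect modification.**

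- Centred factor: ratio 1.0.
- Reference-coded binary factor with prevalence p: the coefficient rests on the share 1 − p, so the ratio is √(1/(1 − p)).
- Uncentred continuous factor: ratio √(1 + (mean/SD)²).

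| Coding | SE ratio | SE | Power for 0.4 |
|---|---|---|---|
| Centred | 1.0 | 0.117 | 0.93 |
| Binary, p = 30% | 1.20 | 0.140 | 0.82 |
| Binary, p = 50% | 1.41 | 0.165 | 0.68 |
| Age uncentred, mean 70, SD 12 | √(1 + 5.83²) = 5.9 | 0.691 | 0.09 |

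**4. How often terms enter by chance.** If no factor matters, six independent tests at 5% admit at least one with probability 1 − 0.95⁶ = 0.26.

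**5. The whole rule, simulated.** Each scenario used 3,000 trials with five sites of 22 control and 44 intervention patients, intracluster correlation 0.10, and least squares with site fixed effects in place of the mixed model. Assumed factors: sex 50%, age 70 (SD 12), employed 35%, severity 6 (SD 4), outside rehabilitation 30%, time since stroke 30 days (SD 15). In the prognostic scenarios the effects per SD were −0.2 for age, −0.3 for severity and 0.1 for time. True average effect 0.40:

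| Scenario | Main effects only: SD of estimate, power | Rule, uncentred: mean, SD, power |
|---|---|---|
| No prognostic factors | 0.11, 0.94 | 0.40, 0.19, 0.83 |
| Prognostic, no modification | 0.11, 0.94 | 0.41, 0.72, 0.09 |
| Prognostic, modification of −0.1 per SD for age and severity | 0.12, 0.94 | 1.14, 0.73, 0.36 |

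The 1.14 is the effect at age 0 and severity 0: 0.4 + 0.1 × 70/12 + 0.1 × 6.05/3.9 = 1.14 (6.05 and 3.9 are the severity mean and SD after truncation at zero). In the two prognostic scenarios about 2.6 interactions entered on average.

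With mean-centred factors the same rule gave a mean of 0.40, SD 0.11 and power about 0.94 in all three scenarios. With no true effect and uncentred factors, the rejection rate was 0.045 to 0.049.

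**The case against.** The strongest reply is that the large losses come from a parameterisation the article never describes. They need uncentred or reference-coded factors and a raw coefficient reported as the primary result. Centring and marginal contrasts are details that an article may leave to an analysis plan, and with centring the average effect comes back at full precision even when modification is real. This stands, and the absence of a centring statement is not by itself the defect.

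Second, the sentence is ambiguous. If it means interactions that are themselves significant, the complaint about the trigger falls away. If it means interactions among factors that do not involve the intervention, the coefficient keeps its meaning. This also stands, so the point is conditional on the reading. Under any of these readings, though, the terms in the model are chosen by p-values.

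Third, exploring contextual factors is a declared aim: the second objective in the Introduction covers it, and the Limitations section returns to it. A reader might infer that these analyses are unplanned. They are not. What is unplanned is which terms end up in the model for the intervention effect.

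A reader might also infer a false-positive problem. The simulation does not support that: under a uniform null the error rate stays near 5%.

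**Conclusion.** The point holds in conditional form, and the plan should be changed. What is fixed badly is the rule itself: it commits to data-selected interactions in the model that is meant to isolate the intervention effect and, on the natural reading, selects on prognostic value and not on evidence of effect modification. The resulting coefficient need not be the average difference that Study Design and Sample Size Estimates describe.

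The size ranges from no loss at all with centred factors, through a 1.2- to 1.4-fold standard error for one reference-coded binary factor at 30 to 50% prevalence, to about six-fold for uncentred age. These figures rest on assumed distributions and, in the simulation, assumed covariate effects. It would be tempting to conclude that the trial will lose its power. The article does not support this, because it does not say how factors will be coded or which quantity will be reported.

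**What to change.** In the Analyses section, replace the interaction sentence with two statements.

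1. The primary intervention effect comes from the linear mixed model with a fixed, pre-listed set of baseline covariates as main effects and no data-selected interactions.
2. A short list of intervention-by-factor interactions, named in advance by the investigators, is examined in separate exploratory models. Factors are centred or an averaged effect is reported, and every listed interaction is reported whatever its p-value.

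This keeps the contextual-factor aim intact. It costs a sentence or two and no data. The Results section says that analysis will not begin before data collection ends, so on the article's account the change can be made before any outcome is analysed.

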### Setting

Five selected sites in Quebec, Canada, will start with a control period (preintervention: usual care) until they independently reach their target sample size; this is expected to take between 12 and 18 months. Participants recruited during this period will belong to the control group. The sites will then enter the intervention period until recruitment completion, which is expected to occur after a further 12 to 18 months. Participants recruited during this second period will belong to the intervention group. Site monitoring will carefully document practices during both trial phases.

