**Health care use**			
		Institut national de santé publique du Québec population questionnaire (section A) [60]	12 and 24 weeks
		Provincial health administrative data	12 and 24 weeks
	Adverse events	Patient’s calendar (collected weekly by a rehabilitation professional): incidence of falls, dizziness, pain (visual analog scale), and fatigue (Borg Rating of Perceived Exertion Scale, 1-10)	Weekly basis up to 12 weeks
	Individual costs	Questionnaire developed by the authors for this study	24 weeks

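### Dichotomous outcomes, including dizziness as an adverse event, are compared by an unadjusted chi-square test although the groups are consecutive, non-randomised recruitment periods

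*Protocol article*

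**What the plan says.** The Analyses section gives two different treatments.

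- For clinical and process outcomes in general it specifies a linear mixed model, with individuals' "data nested into a study site, to isolate the effect of the intervention on both clinical and process outcomes from other changes" occurring during the trial. Sex, age, employment before the stroke, stroke severity, rehabilitation received elsewhere and time since stroke "will be considered in regression models as potential confounders".
- For binary outcomes it says: "Presence of dichotomous stroke outcomes (eg, dizziness) will be compared between study groups using a chi-square test". No adjusted, stratified or exposure-based analysis is stated for them.

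Dizziness appears in Table 1 as an adverse event, taken from this source: "Patient’s calendar (collected weekly by a rehabilitation professional): incidence of falls, dizziness, pain" and fatigue, weekly for up to 12 weeks.

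On design, the article says: "An interrupted time series design with a convergent qualitative component is proposed to test the effectiveness of the intervention". It adds that "such design will accommodate pre-existing trends and control for possible variations within and among sites". Under Setting, the five sites "will start with a control period (preintervention: usual care) until they independently reach their target sample size"; patients recruited afterwards form the intervention group. Sample Size Estimates gives 110 control and 220 intervention patients and assumes, for the primary outcome, "6) intracluster correlations of 0.10".

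**The concern.** In a randomised trial a plain chi-square test on adverse-event proportions would be unremarkable. Here group membership is decided by when the patient was recruited, and control comes first at every site. The article recognises the consequence: it names confounders and chooses a model meant to separate the intervention from other changes. That protection is dropped for dichotomous outcomes. A linear mixed model is not built for them, and the chi-square sentence assigns them elsewhere by name.

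At stake is at least part of the between-group safety comparison. A change in severity, age or referral pattern between periods could make telerehabilitation look more harmful than it is, or could mask real harm. Two further questions arise: whether ignoring site distorts the error rate, and whether any recorded event during follow-up is a fair measure if patients are recorded for different numbers of weeks.

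**Working it through.** The article gives no figure for the binary comparison, so there is none to reproduce. From the document: 5 sites, 110 versus 220 patients, two-sided 5%, ICC 0.10 (stated for the primary outcome). Event rates, case-mix shift, stability of site effects, ratios by site and weeks observed are not given; they are assumed below and varied.

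**1. Case mix.** Assume risk 20% in milder and 40% in severe patients, with no treatment effect.

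- Control period, 40% severe: 0.6 × 0.20 + 0.4 × 0.40 = 0.28.
- Intervention period, 60% severe: 0.4 × 0.20 + 0.6 × 0.40 = 0.32.
- Pooled rate: (110 × 0.28 + 220 × 0.32)/330 = 0.307. SE under the null: √(0.307 × 0.693 × (1/110 + 1/220)) = 0.0538. Unpooled SE: √(0.28 × 0.72/110 + 0.32 × 0.68/220) = 0.0531.
- Chance of a significant excess in the intervention group: Φ((0.04 − 1.96 × 0.0538)/0.0531) = Φ(−1.23), about 11%, where 2.5% would be expected in that direction.

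With a smaller shift, to 50% severe, the rates are 28% versus 30% and this chance is about 5.5%. The bias in the estimate (4 or 2 percentage points) does not shrink with sample size.

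**2. Site.** Let CAC be the correlation of a site's effect between its two periods. With exact 2:1 recruitment at each site, the true variance relative to the variance assumed by the chi-square test is

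[(1 − ρ)(1/110 + 1/220) + 2ρ(1 − CAC)/5] / (1/110 + 1/220).

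With ρ = 0.10 and 1/110 + 1/220 = 0.01364:

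- CAC 1: 0.01227/0.01364 = 0.90, type I error 3.9%
- CAC 0.9: 0.01627/0.01364 = 1.19, 7.3%
- CAC 0.8: 0.02027/0.01364 = 1.49, 10.8%
- CAC 0.5: 0.03227/0.01364 = 2.37, 20.3%

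Simulation of the chi-square test under no effect (30% event rate, ICC 0.10, 20,000 runs per cell):

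| Recruitment by site (control; intervention) | CAC 1 | 0.9 | 0.8 | 0.5 |
|---|---|---|---|---|
| 22 each; 44 each | 4.1% | 7.2% | 11.5% | 20.4% |
| 30,26,22,18,14; 36,40,44,48,52 | 6.7% | 9.9% | 13.1% | 22.0% |
| 40,30,20,10,10; 20,30,40,60,70 | 18.9% | 21.3% | 23.0% | 29.0% |

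The first cell matters most: every site contributes to both periods, so a stable site effect largely cancels.

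**3. Does adjusting for site cure this?** It removes the part due to unequal ratios, because each site is then compared with itself. It does not remove the part due to site-by-period change. In a simulation on the logit scale (22/44 per site, 30% prevalence, stable site SD 0.3), logistic regression with fixed site effects rejected 10.9% against 10.3% for chi-square at a site-by-period SD of 0.27, and 16.9% against 16.0% at SD 0.40. These settings imply ICCs of about 0.05 and 0.07 (for example (0.09 + 0.073)/(0.163 + 3.29) = 0.047), so they illustrate the mechanism and are not the protocol's 0.10.

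**4. Weeks recorded.** Assume a weekly risk of 3% in both groups. The probability of any event is 1 − 0.97^w: 21.6% at 8 weeks, 26.3% at 10, 30.6% at 12. With the control group recorded for the shorter time, 8 versus 12 weeks would be declared different about 40% of the time and 10 versus 12 about 12%, with no true difference.

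**The case against.** The strongest reply has four parts.

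- **The outcomes are secondary.** The primary outcome is minutes of exercise, and the scale outcomes fall under the mixed model. Simple tests on adverse events are common in condensed articles, and covariate sets and offsets are often left to an analysis plan. The limited scope stands and keeps this below the level of a threat to the primary result. But the article does not leave the method open; it names an unadjusted test.
- **Site differences will be visible**, because outcomes are to be summarised by group and site. True, but a summary does not adjust a comparison.
- **Clustering.** A reader might infer from the assumed ICC of 0.10 that the chi-square test must have an inflated type I error. The document does not support that. With stable site effects and 2:1 at each site the test is near nominal or slightly conservative, and the article reports neither site-by-period variation nor unequal ratios. Independent attainment of targets and retraining of teams between periods make both plausible, not established. Nor can the 10-20% figures justify a site term alone, since it would not remove inflation due to site-by-period change.
- **Follow-up.** A reader might also infer that unequal recording has biased the event comparison. The article says only that recording runs up to 12 weeks and assumes under 5% loss; nothing says that weeks recorded differ by group.

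**Conclusion.** The point holds in a limited form. The article assigns dichotomous outcomes to a test with no control for confounding, in a design where its own text calls for such control. That lack applies whatever the site correlation turns out to be. Its size depends on how far case mix drifts: 4 percentage points of spurious difference (28% versus 32%) under the assumed severity shift, 2 points under half that shift, in either direction.

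The error-rate consequence of ignoring site is conditional: about 4-5% in the favourable case, and roughly 7-20% from either site-by-period change or unequal ratios alone, over the ranges tried. Unequal weeks are a risk to guard against. All these magnitudes rest on assumed event rates. The matter should be corrected, but it concerns secondary and safety outcomes only.

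**What to change.** In the Analyses section, replace the chi-square sentence as follows.

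- Make the main analysis of dichotomous outcomes a logistic or log-binomial regression adjusted for site and the confounders already listed. With only five sites, enter site as fixed effects or use a small-sample correction.
- Include a site-by-period random effect, or a sensitivity analysis that allows for site-by-period variation.
- Report adjusted ratios with confidence intervals.
- For calendar events such as falls and dizziness, account for weeks observed: a rate model with log weeks as offset if counts are recorded, or a weekly repeated binary model if only presence is recorded. The article does not say which is recorded.
- Keep the chi-square test as descriptive only.

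The cost is analysis wording. Calendars are already planned weekly, and the Results section says analysis will not begin before data collection ends. The downsides: sparse events may force a smaller covariate set; allowing for site-by-period variation widens the intervals, and five sites estimate that variation poorly; and adjustment for the listed factors does not remove unmeasured changes over calendar time.

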### Primary Outcome

The choice of the primary outcome, patient adherence to the stroke rehabilitation plan at 12 weeks, was identified through a pilot study previously conducted by our research team as the most meaningful outcome and to better document the reason why telerehabilitation might be effective. Adherence to telerehabilitation has been operationalized in many different ways across studies [6,51]. We will define adherence as time spent (in minutes) doing any stroke rehabilitation exercises (online + offline). This includes, but is not limited to, physical, writing, and speech therapy as well as mental health–related exercises recommended by the rehabilitation professional. Online session time will be recorded through the telerehabilitation platform. Offline time will include face-to-face sessions doing rehabilitation as well as time exercising on one’s own as instructed by the rehabilitation professional. Offline sessions completed at home will be captured with the use of a journal and recorded by one of the rehabilitation professionals each week. This monitoring step has been used as a method of quality assurance by other scholars in stroke research [52]. Patients’ adherence to a rehabilitation program will also be measured by the Stroke Rehabilitation Exercise Adherence Measure (StREAM) questionnaire at weeks 4, 6 (to allow for test-retest reliability assessment), and 12 [53]. Moreover, health care professional perception of the participants’ adherence to the rehabilitation program will be evaluated on a numerical 10-point rating scale each week during the intervention period.

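### The missing-data check pairs two analyses that normally share one assumption, so for an adherence outcome their agreement would not show that the result is robust.

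*Protocol article*

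**What the plan says.** In the protocol article, the Primary Outcome section sets the endpoint: "We will define adherence as time spent (in minutes) doing any stroke rehabilitation exercises (online + offline"). It names three sources of minutes. The first is the platform: "Online session time will be recorded through the telerehabilitation platform". The second is face-to-face sessions. The third is exercise done at home: "Offline sessions completed at home will be captured with the use of a journal and recorded by one of the rehabilitation professionals each week".

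The Analyses section says: "Statistical analysis of the data will follow intention-to-treat principles". On missing values it says: "Multiple imputation will be considered if missing data represent more than 10% of a given variable". It then announces a sensitivity analysis for missing data "with a multiple imputation statistical technique and without imputation (ie, available case analyses), as well as for outlying observations". It names no scenario in which missing minutes are lower than observed ones, and it does not give the assumption behind the imputation.

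The article does not say whether weeks after a patient stops rehabilitation count as 0 minutes or as missing. Its only attrition figure is in Sample Size Estimates: "a <5% loss to follow-up".

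**The concern.** A sensitivity analysis should vary the assumption that is most in doubt. Here that is whether missing minutes look like observed minutes. Disengagement lowers the outcome and can also end the weekly contact at which the journal is recorded. The article's Background in the Abstract already describes adherence to stroke rehabilitation as suboptimal, so some stopping is to be expected.

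Available-case analysis uses only what was recorded. Multiple imputation in its usual form draws missing values from patients with similar covariates. Neither represents a patient whose minutes are missing because they fell. If both give the same answer, a reader would take the result as robust although this mechanism was never tested.

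Unequal missingness between the phases is plausible from the design. Control patients have no telerehabilitation, so their minutes come from face-to-face sessions and the journal. In the intervention phase at least 80% of the plan is expected to be telerehabilitation, which the platform logs. Stopping may therefore leave different traces in the two phases, and unequal missingness is the case that distorts the treatment difference.

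**Working it through.** The plan gives no figure on this point to reproduce. The check asks whether the two named analyses can agree and both be wrong, and by how much.

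**Inputs from the article:** 110 control and 220 intervention patients, and a standardised effect of 0.4 (Sample Size Estimates).

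**Assumptions, not in the article:** control mean M_C = 1,000 minutes over 12 weeks and SD 400, so the intervention mean without stopping is M_I = 1,000 + 0.4 × 400 = 1,160. A share p of each group stops, truly reaches a fraction f of its minutes, and has its total treated as missing. The imputation model contains group and one covariate unrelated to stopping.

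**Formulas.** The true group mean is M × [1 − p(1 − f)], while both analyses estimate M. The mean is therefore overstated by M × p × (1 − f), and the error in the difference is (1 − f) × (M_I × p_I − M_C × p_C).

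With f = 0.5:
- 5% control and 15% intervention stopping: 0.5 × (1,160 × 0.15 − 1,000 × 0.05) = 87 − 25 = +62 minutes.
- 15% control and 5% intervention stopping: 0.5 × (1,160 × 0.05 − 1,000 × 0.15) = 29 − 75 = −46 minutes.
- 5% in both: 29 − 25 = +4 minutes.

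**Simulation** (linear model, 10 imputations, 600 replicates; averages in minutes; AC = available-case, MI = multiple imputation):

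| Stopping, control / intervention | f | Intervention mean: true / AC / MI | Difference: true / AC / MI |
|---|---|---|---|
| 5% / 5% | 0.25 | 1115.0 / 1159.3 / 1159.3 | 150.6 / 158.0 / 158.1 |
| 5% / 5% | 0.5 | 1131.9 / 1160.8 / 1160.8 | 156.7 / 161.1 / 161.1 |
| 10% / 10% | 0.5 | 1103.2 / 1162.1 / 1162.0 | 153.4 / 161.0 / 160.8 |
| 20% / 20% | 0.5 | 1046.1 / 1161.6 / 1161.5 | 143.1 / 159.4 / 159.8 |
| 5% / 15% | 0.5 | 1073.3 / 1160.8 / 1161.3 | 97.8 / 159.8 / 160.1 |
| 15% / 5% | 0.5 | 1133.1 / 1161.7 / 1161.6 | 205.6 / 159.9 / 160.1 |
| 10% / 20% | 0.5 | 1043.3 / 1159.0 / 1158.9 | 90.6 / 156.9 / 156.5 |

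On average AC and MI differ by at most 0.5 minutes in every row. At f = 0.5 and equal stopping, both overstate the intervention mean by about 29, 59 and 115 minutes at 5%, 10% and 20%, and the difference by only about 4, 8 and 16 minutes. With unequal stopping the difference is overstated by about 62 minutes (62/160 = 39% of the target difference) or understated by about 46 minutes (46/160 = 29%).

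**If stopping stayed within 5% in each phase.** The largest errors at f = 0.5 arise when only one group stops. They are 1,160 × 0.05 × 0.5 = 29 minutes too high (29/400 = 0.07 SD) or 1,000 × 0.05 × 0.5 = 25 minutes too low (25/400 = 0.06 SD).

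**If weeks after stopping are recorded as zeros.** Nothing is missing for these patients, and the error is 0.

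**The case against.** The strongest objection is that the article never says weeks after stopping are missing. The outcome is minutes actually spent, so a patient who stops has a true value of 0 for those weeks, and under intention to treat that is simply the patient's value. An unattended platform or face-to-face session can be an observed zero. Only home exercise depends on the journal. This stands, and it makes the concern conditional. A reader might infer that the plan credits patients who stop with the minutes of those who continue. The documents do not support that as a fact.

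Second, available-case analysis need not drop such a patient. A weekly model keeps the earlier weeks, and summing recorded minutes would give the true total for someone who really did nothing afterwards. The imputation model is also open. Earlier minutes, the adherence questionnaire at weeks 4, 6 and 12, and the weekly professional ratings could all serve as predictors and narrow the gap. This stands too. The simulation shows a plain imputation model and voided totals, which is the unfavourable case, and the agreement between its two methods follows from that set-up.

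Third, the coding rule and the imputation model may be in an analysis plan that is not shown. Their absence from the article is therefore not the fault raised here. The point concerns the pair of analyses that the article does name for this purpose.

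Fourth, loss to follow-up is assumed to be below 5%, which would keep the error small. That holds only in part. Ceasing to exercise or to return a journal is not the same as being lost to follow-up, and the Analyses section itself provides for more than 10% missing on a variable.

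**Conclusion.** The point holds in a conditional form. Comparing multiple imputation with available cases, as normally run, does not test whether minutes are missing because they are low, so agreement between the two is no evidence of robustness for this outcome. Where weeks after stopping are treated as missing, mean adherence is overstated in each group with stopping.

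A reader might go further and conclude that the intervention effect will be inflated. That does not follow. The error can take either sign depending on which phase has more stopping, and it is small when stopping is equal. The size in this trial is unknown. Every figure in minutes rests on the assumed mean, SD, stopping rates and fraction of minutes completed. This is an inexpensive improvement to the plan and does not show that its result will be wrong.

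**What to change.** 1. State that weeks after documented stopping of rehabilitation count as 0 minutes in the primary outcome.
2. For the remaining missing weeks, add to the stated pair a delta-adjusted multiple imputation. Lower the imputed minutes stepwise from 0% to 100%, separately in the control and intervention groups, and report the reduction at which the conclusion changes.
3. Keep the available-case analysis as a description, not as the evidence of robustness.

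The cost is a few sentences and a little programming, with no additional patients. Stop dates and reasons must be recorded. The Results section reports 37 patients enrolled by July 2021, with control collection under way and analysis deferred until all data are in, so this recording should start early. The downside is that setting minutes to zero is too severe for patients who keep exercising without recording it, so the zero-minute scenario should be presented as a conservative bound.
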